## Abstract

**Introduction:**

Delirium, a clinical manifestation of acute encephalopathy, is associated with extended hospitalisation, long-term cognitive dysfunction, increased mortality and high healthcare costs. Despite intensive research, there is still no targeted treatment. Delirium is characterised by electroencephalography (EEG) slowing, increased relative delta power and decreased functional connectivity. Recent studies suggest that transcranial alternating current stimulation (tACS) can entrain EEG activity, strengthen connectivity and improve cognitive functioning. Hence, tACS offers a potential treatment for augmenting EEG activity and reducing the duration of delirium. This study aims to evaluate the feasibility and assess the efficacy of tACS in reducing relative delta power.

**Methods and analysis:**

A randomised, double-blind, sham-controlled trial will be conducted across three medical centres in the Netherlands. The study comprises two phases: a pilot phase (n=30) and a main study phase (n=129). Participants are patients aged 50 years and older who are diagnosed with delirium using the Diagnostic and Statistical Manual of Mental Disorders, Fifth Edition, Text Revision criteria (DSM-5-TR), that persists despite treatment of underlying causes. During the pilot phase, participants will be randomised (1:1) to receive either standardised (10 Hz) tACS or sham tACS. In the main study phase, participants will be randomised to standardised tACS, sham tACS or personalised tACS, in which tACS settings are tailored to the participant. All participants will undergo daily 30 min of (sham) stimulation for up to 14 days or until delirium resolution or hospital discharge. Sixty-four-channel resting-state EEG will be recorded pre- and post the first tACS session, and following the final tACS session. Daily delirium assessments will be acquired using the Intensive Care Delirium Screening Checklist and Delirium Observation Screening Scale. The pilot phase will assess the percentage of completed tACS sessions and increased care requirements post-tACS. The primary outcome variable is change in relative delta EEG power. Secondary outcomes include (1) delirium duration and severity, (2) quantitative EEG measurements, (3) length of hospital stay, (4) cognitive functioning at 3 months post-tACS and (5) tACS treatment burden. Study recruitment started in April 2024 and is ongoing.

**Ethics and dissemination:**

The study has been approved by the Medical Ethics Committee of the Utrecht University Medical Center and the Institutional Review Boards of all participating centres. Trial results will be disseminated via peer-reviewed publications and conference presentations.

**Trial registration number:**

NCT06285721.

STRENGTHS AND LIMITATIONS OF THIS STUDYThis is a randomised, double-blind, sham-controlled trial to evaluate transcranial alternating current stimulation (tACS) as treatment for delirium.The analysis of electroencephalography (EEG) before and after tACS will provide insights into the neurophysiological effects of tACS in delirium.An inital pilot phase will assess the feasibility of tACS in a delirium population.This study incorporates a personalised treatment arm that tailors tACS settings to an individual participant.Applicability to hyperactive delirium may be limited due to the requirement for patients to complete EEG assessments.

Recent studies in healthy individuals have demonstrated the potential of transcranial alternating current stimulation (tACS) in modulating brain activity by entrainment of specific cortical rhythms based on the applied stimulation frequency.^25^,^27^ The administration of tACS is suggested to phase-lock large populations of neurons in the superficial layers of the cerebral cortex, inducing neural synchronisation in the corresponding frequency, and changing brain connectivity.^28 29^ Studies on healthy individuals have revealed that tACS applied in the alpha frequency range can augment alpha activity and functional brain connectivity,^2530^,^33^ both affected during delirium.^34^ Furthermore, a meta-analysis has indicated a clear beneficial effect of tACS on cognition in other populations, including improvements in attention and working memory,^35^ which are cognitive domains also affected during delirium.^1^ Interestingly, a recent study with healthy volunteers showed that alpha-tACS not only augments alpha activity but also strengthens connectivity within the DMN,^25^ the primary network disturbed during delirium.^22 23^ Additionally, oscillatory entrainment can have cross-frequency effects,^30 36^ meaning that tACS applied within the alpha frequency range can lead to a decrease in relative delta power. Taken together, tACS might be able to reduce delta activity, reinforce alpha activity and connectivity in brain regions that show altered connectivity during delirium,^22 23^ potentially offering therapeutic benefits.

When applying tACS as a potential treatment for delirium, the most straightforward approach is to apply tACS in the alpha frequency range, targeting both reduced alpha power and functional connectivity seen in delirium.^15^,^18^ However, numerous approaches in terms of stimulation location and frequency are possible, which might be equally or more effective in treating delirium than alpha-tACS. Incorporating functional brain connectivity changes of individual patients into personalised treatment could improve treatment effectiveness, reduce adverse effects, decrease the need for trial and error in clinical trials and enhance our understanding of the mechanisms underlying treatment effects.^37^ The use of computational models may allow one to infer how modifications of neuronal properties might influence emergent neuronal activity and treatment response.^38^ A promising type of computational model is the neural mass model, which models brain activity of large populations of neurons.^39^ Using a network of coupled neural masses, neuronal activity similar to an encephalopathic EEG has been simulated.^40^ Building on this, this study will apply neural mass modelling of individual functional connectivity changes in a virtual trial to optimise treatment settings.

In the current trial, we will evaluate whether tACS normalises brain activity, specifically relative delta power, in delirium. To date, no randomised controlled trials (RCTs) investigated tACS as treatment for delirium, highlighting significant gaps in our understanding of the feasibility, effectiveness and the most effective application strategies. Therefore, the trial will begin with a pilot phase aimed to assess feasibility. On successful completion of the pilot phase, the main study phase will commence with three study arms to assess the efficacy of tACS in reducing relative delta power: a standardised treatment arm, a sham control arm and a personalised treatment arm based on a computational model and virtual trial. We hypothesise that both standardised and personalised tACS will decrease relative delta power compared with sham tACS in delirium patients. By adopting this two-step approach, this study aims to evaluate the feasibility as well as the effectiveness of tACS in patients with delirium.

## Methods and analysis

### Study objectives

For the pilot phase, the primary objective is to evaluate the safety and tolerability of tACS in patients with delirium. The main study phase aims to determine the efficacy of a single session of standardised or personalised tACS in reducing EEG relative delta power in patients with delirium. Secondary objectives include assessment of the impact of daily standardised or personalised tACS compared with sham on the duration and/or severity of delirium, the length of hospital stay and cognitive functioning 3 months after the initial tACS session.

### Study design and setting

This study is a double-blind, RCT conducted across three medical centres in the Netherlands: the University Medical Center (UMC) Utrecht, Radboud UMC and HagaZiekenhuis. To assess safety and feasibility of tACS in delirious patients, the study will start with a pilot phase in which 30 patients will be randomised in a 1:1 ratio to receive daily either standardised active tACS or sham treatment for a maximum of 14 days, or until resolution of delirium or hospital discharge.

On completion of the pilot phase, the main study phase will begin, introducing the personalised treatment arm. Criteria for continuing to the main study phase are defined under outcomes. All patients from the pilot phase will be included in the main study analyses. Randomisation weights will be recalculated, and participants will be allocated in an overall 1:1:1 ratio to receive either standardised tACS, personalised tACS, or sham treatment (ie, combining personalised sham and standardised sham tACS into one arm). The baseline visit will include delirium assessment using the Delirium Interview,^41^ administered by a trained researcher, and reviewed by an expert delirium panel. Furthermore, information will be collected from the electronic patient record and the Clinical Frailty Scale^42^ will be evaluated. After these assessments, the first treatment session starts which includes a 64-channel EEG measurement before and after the first tACS or sham treatment. Also, a questionnaire on sensation to assess possible adverse events (AEs) of tACS, a questionnaire on feasibility and questionnaire on blinding and subjective treatment experiences (online supplemental appendix 1) will be administered. Following this, daily tACS or sham treatment visits and delirium assessments will take place for a maximum of 14 days, or until resolution of delirium or hospital discharge, whichever comes first. To account for fluctuations in delirium symptoms, resolution of delirium is defined as two consecutive negative delirium assessments. The treatment phase will end with a close-out visit including a follow-up 64-channel EEG and administration of the questionnaires on sensation, blinding and subjective treatment experiences. A brief cognitive assessment using the Telephone Interview for Cognitive status, modified version (TICS-M)^43 44^ is planned at 3 months after the first tACS session. The study design is illustrated in figure 1, and the study schedule is presented in table 1.

**Figure 1 F1:**
[figure not shown]
Study flow chart. EEG, electroencephalography; tACS, transcranial alternating current stimulation; T, treatment; V, visit.

**Table 1 T1:** Overview study procedures

Procedures (time needed)	Baseline visit (V1)	First treatment visit (T1)	Additional treatment visits (T2 up to T14)	Post-treatment visit (V2)	Follow-up visit (V3)
Medical history*	X				
Physical health*	X				X
Current medication use*	X	X	X	X	X
Clinical Frailty Scale*	X				
Sensation questionnaire (5 min)		X		X	
Blinding and subjective treatment experience (1 min)		X		X	
Feasibility questionnaire (5 min)		X			
Delirium interview (10 min)	X				
ICDSC (10 min)	X	X	X	X	
DOSS (5 min)†	X	X	X	X	
TICS-M (10 min)					X
EEG (40 min)	X‡	X		X	
tACS (30 min)		X	X		
Estimated total duration	25 or 60 min‡	95 min	45 min	65 min	15 min

* This information will be recorded as part of standard clinical care, and missing information will be requested via family and will therefore not require additional time.

† Only non-intensive care unit () patients will be assessed using the DOSS.

‡ Only the group randomised to personalised tACS will receive an EEG during the baseline visit.

DOSS, Delirium Observation Screening Scale; EEG, ElectroencephalogramICDSC, Intensive Care Delirium Screening Checklist; tACStranscranial altering current stimulationTICS-M, Telephone Interview for Cognitive status, modified version

### Sample size and statistical power

The sample size calculation is based on data obtained from a previous study that examined EEG findings in both delirious and non-delirious patients.^15^ In this study, patients with delirium showed a median relative delta power of 0.59 (IQR 0.47–0.71), while those without delirium had a median of 0.20 (IQR 0.17–0.26), resulting in an effect size of 0.39 (0.20–0.59). This study excluded patients in whom the diagnosis delirium was not certain, which may have inflated the effect size. It is therefore anticipated that both standardised and personalised tACS will lead to a more modest decrease of 0.15 in relative delta EEG power poststimulation compared with prestimulation measurements. We hypothesise that personalised tACS may be superior to standardised tACS in reducing relative delta power. However, the lack of data to support this claim necessitates assuming equal effectiveness for both arms in the sample size calculation. Based on these assumptions, a sample size of 159 participants (ie, 53 per group) was estimated using G*Power 3.1. This estimation considered an effect size of 0.15 with a SD of 0.3, an alpha of 0.05 and 80% statistical power. Patients who do not complete the initial tACS session with EEG recordings will be replaced, as well as patients who withdraw consent.

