#### Sham stimulation

The procedure for sham stimulation will be identical to either standardised or personalised tACS, except for the electrical current administered. After the 5-digit pin code is entered, which enables sham stimulation, the tACS device will ramp up to 2.0 mA peak to peak for 30 s, stimulate for 60 s and ramp down for 30 s to 0 mA. This mimics the perception of actual tACS stimulation and improves blinding. To evaluate the effectiveness of blinding, both the participant and the researcher will be asked to guess the group allocation after the first and last treatment session (online supplemental appendix 1).

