### Statistical analysis

For the analysis of the primary study parameter, a per-protocol analysis will be used. The sole criterion for inclusion in the analysis is that a participant has completed the initial tACS session and EEG recordings. Changes in relative delta power will be assessed using separate linear mixed models for standardised and personalised tACS compared with sham, with relative delta power as the dependent variable, time*group and study centre as fixed factors, and participant as a random factor. Data analysis will be performed blinded for treatment allocation. A significance level of p=0.05 (two-tailed) will be applied. To retain sensitivity to detect potential effects in this novel area of research, no adjustment for multiple comparisons will be made. In cases of deviations from the linear mixed model, robust models and non-parametric alternatives will be considered. Subgroup analysis will be conducted by including additional fixed factors to the mixed models, such as delirium aetiology, sex and age. Functional outcomes, along with other quantitative EEG measurements and cognitive outcomes, will be analysed using non-parametric or parametric tests depending on the distribution of scaled test results. Blinding success for participants as well as researchers will be tested using a χ^2^ test.

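### The stated 80% power does not apply to the primary active-versus-sham contrast: on the plan's inputs 53 per arm gives about 72%, and only if sham does not change

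*Protocol article*

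**What the plan says.** The section on sample size and statistical power in the protocol article expects that both active arms "will lead to a more modest decrease of 0.15 in relative delta EEG power poststimulation compared with prestimulation measurements". It gives no expected change in the sham arm and no active-minus-sham difference. The inputs are then listed: "This estimation considered an effect size of 0.15 with a SD of 0.3, an alpha of 0.05 and 80% statistical power". The result is that "a sample size of 159 participants (ie, 53 per group) was estimated using G*Power 3.1". For want of data on personalised stimulation, this "necessitates assuming equal effectiveness for both arms in the sample size calculation". The section does not name the test chosen in G*Power, and it does not say whether 0.3 is the SD of the pre-to-post change or of a single measurement.

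The statistical analysis section fixes the primary test. Change in relative delta power is assessed with "separate linear mixed models for standardised and personalised tACS compared with sham", with time*group and study centre as fixed factors and participant as a random factor. On the error rate: "A significance level of p=0.05 (two-tailed) will be applied". The hypothesis at the end of the introduction is also a comparison of each active arm with sham.

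The sample size section also gives the earlier study's difference between delirious and non-delirious patients as "resulting in an effect size of 0.39 (0.20–0.59", with the bracket closed after the second figure.

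**The concern.** The power statement and the primary test do not describe the same quantity, in two respects.

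- **The test.** The analysis makes two separate pairwise comparisons with sham. If the 159 comes from a different kind of test, the 80% does not carry over to either comparison.
- **The effect.** A time*group term estimates the active change minus the sham change. The 0.15 is described as a fall from before to after stimulation in the active arms. The two agree only if the mean sham change is zero, and the text does not say that this is assumed.

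The stake is how a non-significant result is read. With 80% stated, a reader would take it as fairly strong evidence against a net effect of 0.15. On the stated inputs the chance of missing that effect is nearer 28% than 20%, and larger if sham patients also improve.

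**Working it through.** **Inputs (protocol article).** Effect 0.15, SD 0.3, alpha 0.05, power 80%, 53 per group and 159 in total (sample size section); two-sided 0.05, each active arm against sham, time*group (statistical analysis section). Standardised effect: d = 0.15/0.3 = 0.5.

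**Step 1: reproduce the 159.** The test is not named, so candidates were tried for 80% power at alpha 0.05.

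| Candidate | Per group | Total | Matches 159? |
|---|---|---|---|
| Three-group omnibus F, f = 0.25 | 53 | 159 | yes |
| Three-group omnibus F, means 0.15, 0.15, 0 (f = 0.236) | 59 | 177 | no |
| Two-sample t, two-sided | 64 | 192 | no |
| Two-sample t, one-sided | 51 | 153 | no |
| Paired t within one arm, SD of change 0.3 | 34 | 102 | no |

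For the match: f = d/2 = 0.25, the conversion for two groups. Noncentrality is N·f² = 159 × 0.0625 = 9.94, with 2 and 156 degrees of freedom, and power is 80.5%. With 52 per group it is 79.7%, so 53 is the smallest group size that reaches 80%. For the plan's own pattern (two equal active arms, sham at zero), f = √0.005/0.3 = 0.236, which is why that row needs 59.

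**Step 2: power of the test the plan runs.** With two time points and complete data, the time*group test in a two-arm model is in effect a two-sample t test on the change scores. With n per arm and net effect δ:

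- noncentrality = (δ/SD of change) × √(n/2), df = 2n − 2
- δ = 0.15, SD of change 0.3, n = 53: 0.5 × √26.5 = 2.574, df = 104, critical value 1.983, power **72%**
- for 80%: n = 64 per arm (80.1%), 192 in total; 63 per arm gives 79.5%
- with 53 per arm, 80% power is reached at a net difference of about 0.165

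**Step 3: what an unstated sham change would do.** The documents give no sham change, so the values below are assumptions. The active fall is held at 0.15, so δ = 0.15 − sham fall, with n = 53 per arm.

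| Sham fall | δ | Power, SD of change 0.3 | Power, SD of change 0.2 |
|---|---|---|---|
| 0 | 0.15 | 72% | 97% |
| 0.03 | 0.12 | 53% | 86% |
| 0.05 | 0.10 | 40% | 72% |

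If sham instead rose by 0.03, δ would be 0.18 and power 86% at SD 0.3.

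**Step 4: which SD is 0.3?** If 0.3 is the SD at one time point and r is the pre-post correlation (assumed), the SD of change is 0.3 × √(2(1 − r)). For δ = 0.15 and n = 53, power is 44% at r = 0 (SD of change 0.424), 72% at r = 0.5 (0.300) and 91% at r = 0.7 (0.232).

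**Step 5: the bracket after 0.39.** The two medians quoted in the same sentence are 0.59 and 0.20, and 0.59 − 0.20 = 0.39. The bracket repeats the medians; it is not an interval for the difference.

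**The case against.** Four points deserve a fair hearing.

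1. **The 80% is not that of a within-arm test.** A reader might infer from the pre-to-post wording that the 80% belongs to a within-arm comparison. The figures do not support that: such a test needs 34 per arm, and 53 would give it 95%. The 159 fits a between-group calculation, in which 0.15 acted as a difference between arms with sham change taken as zero. The drop from 80% to 72% therefore comes from the omnibus test and the two-group f conversion, and is present even when sham does not change. This stands.

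2. **A fall in the sham arm is not shown.** The primary outcome is EEG just before and just after one 30-minute session. Fluctuating symptoms add variance but need not shift the mean in one direction. Treatment of underlying causes is an entry condition and says little about a single session. In the sham procedure "the tACS device will ramp up to 2.0 mA peak to peak for 30 s, stimulate for 60 s and ramp down for 30 s", but nothing in the document says that this lowers delta power. This stands: the rows for 0.03 and 0.05 are a sensitivity range, not a forecast.

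3. **The trial may be adequately powered.** The IQR of 0.47–0.71 in delirious patients implies a cross-sectional SD of about 0.24/1.349 = 0.18 under normality. If that were the SD at each time point, a net 0.15 would have 86% power at r = 0 and 99% at r = 0.5. This also stands, but it rests on an SD other than the one the plan used. It is a reason to state which SD is meant, and it does not rescue the 80% as printed.

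4. **The bracket is clerical.** A reader might take 0.20 as a lower confidence bound that makes 0.15 look cautious. The text does not argue that way: it justifies the smaller effect by the earlier study's exclusion of uncertain diagnoses, and the bracket is not an input to the calculation.

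**Conclusion.** The point holds in this form. The 80% power for 53 per group does not apply to the primary contrast of each active arm with sham. On the plan's inputs, with 0.3 read as the SD of change and no sham change, that contrast has about 72% power, and 80% would need 64 per arm. That an omnibus F test with f = 0.25 produced the 159 is an inference from an exact numerical match, since the document names no test; the 72% does not depend on it.

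The pre-to-post wording is a second, separate gap. It lowers power further only if sham also falls, by an amount the documents do not give.

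It would go too far to conclude that the trial is underpowered. With an SD of change of 0.2, power is 97% at zero sham change and still 72% at a sham fall of 0.05. What can be said is that the stated power is wrong for the stated inputs, and that the text does not let a reader work out the right one.

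**What to change.** In the sample size section:

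- define 0.15 as the active-minus-sham difference in pre-to-post change in relative delta power, the quantity that time*group estimates;
- state the assumed sham change, including zero if that is the assumption;
- say whether 0.3 is the SD of the change or of a single measurement, and in the latter case give the assumed pre-post correlation;
- replace the 80% with the power of the pairwise two-sided time*group contrast at 53 per arm, about 72% at an SD of change of 0.3 and zero sham change;
- add a short sensitivity table, for example sham falls of 0, 0.03 and 0.05 at SDs of change of 0.3 and 0.2;
- as a minor correction, label the bracket (0.20–0.59) as the two group medians.

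The cost is a few sentences and one table, with no more patients and no change of analysis. The downside is a stated power that is conditional and looks less favourable. Recruitment is still under way, so the assumptions can be set down before results are known.

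### The stated 80% power with 53 patients per group does not follow from the planned two-tailed comparisons with sham; with the stated inputs it is about 72% if 0.3 is the SD of the pre-post change.

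*Protocol article*

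**What the plan says.** The section on sample size and statistical power in the protocol article reports that "a sample size of 159 participants (ie, 53 per group) was estimated using G*Power 3.1". It lists the inputs: "This estimation considered an effect size of 0.15 with a SD of 0.3, an alpha of 0.05 and 80% statistical power". The 0.15 is described as a "decrease of 0.15 in relative delta EEG power poststimulation compared with prestimulation measurements" and is expected in both active arms, because the lack of data on superiority "necessitates assuming equal effectiveness for both arms in the sample size calculation". The section does not name the test entered in G*Power, say whether it was one- or two-tailed, or say whether 0.3 is the SD of the change or of a single recording.

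The section on statistical analysis fixes the primary analysis: "Changes in relative delta power will be assessed using separate linear mixed models for standardised and personalised tACS compared with sham". The models contain a time-by-group term, study centre, and a random participant effect. Further, "A significance level of p=0.05 (two-tailed) will be applied", and "no adjustment for multiple comparisons will be made". No three-group test is described for the primary outcome.

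**The concern.** A stated power belongs to one particular test. Here the inputs and the test are both given, so one can be checked against the other, and they disagree. An effect of 0.15 with SD 0.3 is a standardised difference of 0.5. A two-sided two-group comparison at 0.05 then needs 64 per group for 80% power, not 53.

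The stake is how a null result will be read. If one active arm does not differ significantly from sham, readers will take it as the result of a comparison with a one-in-five chance of missing the planned effect. On the stated inputs, with 0.3 as the SD of change, that chance is nearer 28% (100% - 72.2%).

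The effect is also defined on a different contrast from the one tested. The 0.15 is a pre-to-post fall within an active arm, whereas the time-by-group term tests the difference in change from sham. The two coincide only if sham patients do not change on average.

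**Working it through.** **Inputs.** From the sample size section: difference 0.15, SD 0.3, alpha 0.05, 53 per group. From the statistical analysis section: two-tailed tests, each active arm against sham, no multiplicity adjustment. With two recordings and only complete pairs analysed, the time-by-group term is in essence a two-sample comparison of the pre-post change, so the noncentral t distribution applies.

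**Reproducing the plan's figure.** Two calculations give exactly 53 per group:

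- *One-way ANOVA, three equal groups, f = 0.25 (that is, d/2).* Noncentrality is f² × N. At N = 159 it is 0.0625 × 159 = 9.94 and power is 80.5%; at N = 156 it is 9.75 and power is 79.7%. So 159 is the smallest total with equal groups that reaches 80%.
- *One-tailed Wilcoxon-Mann-Whitney, d = 0.5, normal parent.* The effective size is n × 3/π. Power is 79.6% at 52 per group and 80.3% at 53, and 3 × 53 = 159.

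A one-tailed t-test comes close but does not match: it needs 51 per group.

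**The planned test, with 0.3 as the SD of the change.**

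- d = 0.15/0.3 = 0.5
- Noncentrality = d × √(n/2) = 0.5 × √26.5 = 2.574, with 104 degrees of freedom and critical value 1.983
- Power at 53 v 53 = 72.2% (73.0% by the normal approximation)
- 63 v 63 gives 79.5% and 64 v 64 gives 80.1%, so 64 per group are needed, 3 × 64 = 192 in total
- Effect detectable with 80% power at 53 v 53: d = 0.549, that is 0.549 × 0.3 = 0.165

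**Expected arm sizes.** The pilot gives 15 patients each to standardised tACS and sham. The main-phase weights 3:4:1:2 apply to 129 patients. Standardised: 15 + 0.3 × 129 = 53.7. Personalised: 0.4 × 129 = 51.6. Sham (both kinds): 15 + (0.1 + 0.2) × 129 = 53.7. Power is 72.8% for standardised and 71.9% for personalised against sham.

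**If 0.3 is the SD of a single recording.** The SD of the change is then 0.3 × √(2(1 − ρ)), where ρ is the pre-post correlation. The document gives no ρ, so these values are assumptions:

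| ρ | SD of change | Power, 53 v 53, two-tailed |
|---|---|---|
| 0 | 0.424 | 44% |
| 0.4 | 0.329 | 64% |
| 0.5 | 0.300 | 72% |
| about 0.59 | 0.272 | 80% |
| 0.7 | 0.232 | 91% |

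**The case against.** **A reader might infer that the sponsor sized a three-group ANOVA.** The match is exact, but the document does not say so. The one-tailed rank test matches just as exactly. The ANOVA reading also requires f to have been set to d/2, although sham at 0 and both active arms at −0.15 with SD 0.3 imply f = 0.236. The origin of 159 is therefore unknown. This does not rescue the 80%: one candidate is an omnibus test that is not planned, and the other is one-tailed, while the plan is two-tailed with non-parametric methods only as a fallback.

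**A reader might infer that the trial is underpowered.** That is not shown. The sample size section's own delirium data (IQR 0.47–0.71) suggest a single-recording SD of about 0.24/1.349 = 0.18 under normality, well below 0.3. With that SD, a difference of 0.15 would have 86% power at ρ = 0 and 99% at ρ = 0.5. The value 0.3 may be deliberately cautious. This objection stands as to the trial's true power. It does not make the stated figure follow from the stated inputs.

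**The 72% rests on reading 0.3 as the SD of change.** This also stands. If 0.3 is a single-recording SD, a correlation of about 0.59 would give 80%, but no correlation is stated. The 72% must therefore be printed as conditional.

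**The remedy is only rewording.** True: patients, analysis and alpha stay the same. But stated power governs how a non-significant arm is interpreted, and recruitment is ongoing, so the correction can be made before the analysis.

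**Conclusion.** The power statement is wrong as written. With the stated inputs, and 0.3 taken as the SD of the pre-post change, each planned two-tailed comparison with sham has 72.2% power at 53 v 53, and about 72–73% with the expected arm sizes. This is roughly 8 percentage points below the stated 80%.

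The result rests on three assumptions: that 0.3 is the SD of change (or, equivalently, a single-recording SD with correlation 0.5), that sham does not change on average, so that 0.15 is also the difference from sham, and that the time-by-group term behaves like a two-sample t-test of change. If 0.3 is a single-recording SD, the power cannot be fixed without a correlation that the document does not give.

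The documents do not establish which G*Power test produced 159, nor that the trial lacks power for the effect it will meet.

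**What to change.** Keep 159 patients and rewrite the sample size paragraph for the test that will be run:

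1. Define 0.15 as the difference between an active arm and sham in the pre-post change.
2. State whether 0.3 is the SD of the change or of a single recording and, in the latter case, the pre-post correlation assumed.
3. Replace 80% with the resulting power. If 0.3 is the SD of change, suitable wording is:

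> With 53 patients per group, each two-sided comparison with sham at alpha 0.05 has 72% power for a between-group difference in change of 0.15 (SD of change 0.3), and 80% power for a difference of 0.165.

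4. Name the test and the sidedness that were entered in G*Power.

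The cost is the rewording and, if 0.3 is the SD of change, a less favourable stated power. No extra patients are needed, and the analysis and alpha do not change. Keeping 80% power at 0.15 on that reading would instead take 192 − 159 = 33 more patients, which this fix does not ask for.
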